## Methods/design

This multicenter study will be conducted in two stages. The first stage will consist of a cross-sectional study within all consecutive patients admitted to the participating EDs following a recent trauma (< 1 month), to systematically measure their risk of PTSD. The second stage will be a prospective cohort study designed to analyze the relationship between PTSD occurrence and its putative predictive factors in a sub-sample of patients randomly selected among those identified as “at moderate or high risk” for developing PTSD at admission to the ED and followed-up for 3 months.

### Study setting

The study will take place in six large EDs of the Auvergne-Rhône-Alpes region of France; the four EDs in Lyon (two at the Edouard Herriot hospital, one in Lyon Sud hospital, and one in Saint Luc Saint Joseph hospital), one in Saint Etienne (North university hospital) and one in Clermont Ferrand (university hospital). The region had 7.878 million inhabitants in 2015 (source Eurostat) and covers urban and rural, economically deprived and non-deprived areas.

### Participant eligibility

The target population will be adults (≤ 70 years of age) visiting the EDs during the 1-month inclusion period who were victims of a recent traumatic event (< 1 month) and willing to participate in the study. The trauma will be defined as a direct exposure, directly witnessing trauma to a third party, or discovering that a traumatic event has happened to a close family member or a close friend. In case of actual death or death threat to a member of the family or a friend, the event(s) must have been violent or accidental. We will also consider the recurrent or extreme occupational exposure to traumatic events (e.g. front-line workers collecting human remains, police repeatedly exposed to explicit child sexual abuse) [4]. Furthermore, participants must be affiliated to the French public health insurance system, and provide written informed consent. In case of an adult under curatorship, the recruiter will seek only his/her consent, the consent of the curator being not mandatory in the French law.

Patients who are either unable to communicate fluently in French or under guardianship, and/or have clinical instability that makes completing the questionnaire(s) impossible (e.g. agitation, critical condition, distorted consciousness, etc.) will not be included in the study.

### Recruitment process

Figure 1 illustrates stages of the study. Initially (for a period of 1 month) each eligible consumer of the assigned EDs will be screened from 08:00 to 24:00/day and 7 days/week, based on inclusion criteria. The screening will be performed by a trained interviewer (research assistant or medical/nurse student), supervised by a psychiatrist or emergency physician. The investigating physician will explain the study to each eligible patient and provide him/her with a written synopsis of the objectives and course of the research (including that they can be drawn at random to receive the questionnaires by an email or postal mail and a telephone follow-up). In case the patient is willing to participate, he/she will date and sign the consent form and a trained interviewer will collect baseline data. Participation in the study will neither change any healthcare required by the patients, nor their right to retract from the study at any time they desire.

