**Discussion:**

This is the first study to assess PTSD predictors prospectively with a biopsychosocial approach within a cohort representative of EDs visitors. The results will inform the development of dedicated interventions to decrease the risk of subsequent PTSD.

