## Objectives

### Primary objectives

The primary objective of the cross-sectional study is to estimate the prevalence of patients with high or moderate risk of developing PTSD in all consecutive cases admitted to the EDs after recent trauma (< 1 month).

The primary objective of the prospective cohort study is to determine predictors of PTSD occurrence at 3 months in a randomly selected sub-sample of patients included in the cross-sectional study and identified as “at moderate or high risk” for developing PTSD at admission to the ED.

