### Sample size

The total number of ED visits in the assigned six centers over a period of 1 month is more than 20,000. We plan to screen around 15,000 patients (75%) with an age range of 18 to 70. Following a traumatic context, 10 to 50% of survivors consult EDs [3, 15, 79, 80]. Considering the most conservative hypothesis (10% of the 15,000 visiting 18–70 year old patients), we estimate that 1500 patients could be included in the study to participate in the cross-sectional part of the study.

The main objective of the cohort study is to identify factors associated with the occurrence of 3-month PTSD. In the literature, incidence of PTSD in various populations and after different types of trauma usually ranges from 30 to 60% [3, 15, 79, 80]. Considering the hypothesis of a 40% incidence of PTSD in the “unexposed” group, the inclusion of 305 patients should allow, with an alpha risk of 0.05, and a power of 80%, to identify factors associated with a relative risk of at least 1.4 [81].

As we anticipate 30% of the subjects may be either lost to follow-up or unwilling to participate at 3 months, we will randomly select a cohort of 400 patients.

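### The primary prevalence is defined in all consecutive ED trauma cases, but screening runs only from 08:00 to 24:00, so patients who arrive and leave overnight cannot be sampled

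*Protocol article*

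**What the plan says.** Three places in the protocol article set the population without any limit on time of day:

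- Primary objectives: the prevalence of high or moderate PTSD risk is to be estimated "in all consecutive cases admitted to the EDs after recent trauma".
- Methods/design: the first stage is "a cross-sectional study within all consecutive patients admitted to the participating EDs following a recent trauma".
- Participant eligibility: the target population is adults "visiting the EDs during the 1-month inclusion period who were victims of a recent traumatic event".

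The discussion part of the abstract adds that predictors will be assessed "within a cohort representative of EDs visitors".

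Recruitment process sets the working hours: eligible patients will be "screened from 08:00 to 24:00/day and 7 days/week". It does not say what happens to patients who came in overnight and are still in the department at 08:00.

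Two sections deal with non-inclusion. The descriptive analysis section attributes possible selection bias to EDs or patients being unwilling, and plans to compare included with not-included patients. The Challenges section attributes non-recruitment to unwillingness or ineligibility. Neither mentions the unscreened hours.

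**The concern.** A consecutive series means that every eligible patient in the period has a chance of entering. With eight unscreened hours each day, one group has none. The main cross-sectional result is a prevalence with a 95% confidence interval. That interval reflects sampling error only. It says nothing about people who were never in the sampling frame, and a larger sample does not reduce that error.

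The gap could be related to the outcome. The Background lists intentional aggression and substance abuse among known predictors of PTSD, and Table 2 includes type and timing of trauma, blood alcohol level and alcohol misuse. It is plausible that these differ between night and day attenders, although the article does not say so. The Background also criticises earlier studies for selection bias, and the Discussion rests generalisability on sample size, so the population that the prevalence refers to should be stated exactly.

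**Working it through.** **1. The plan's own number.** The Sample size section states: "The total number of ED visits in the assigned six centers over a period of 1 month is more than 20,000". It continues: "We plan to screen around 15,000 patients (75%) with an age range of 18 to 70". It then takes 10% as trauma cases.

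- 20,000 × 0.75 = 15,000
- 15,000 × 0.10 = 1500, which matches the stated figure.

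The 75% is attached to the age range. No allowance for unscreened hours is stated.

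**2. Coverage of the clock.** Screened hours are 16/24 = 66.7% and unscreened hours 8/24 = 33.3%. This is a share of hours, not of patients.

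**3. Who is certain to be missed.** The window limits when a patient can be approached, not when the patient arrived. A patient who arrives at 04:00 and is still there at 08:00 could be screened. Only those who arrive and leave between 00:00 and 08:00 have no chance of selection.

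**4. Sampling error at N = 1500.** Half-width = 1.96 × √(p(1 − p)/1500).

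- p = 0.30: 1.96 × √(0.21/1500) = 2.3 points
- p = 0.50: 1.96 × √(0.25/1500) = 2.5 points

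**5. Possible bias.** Bias = s × d. Here s is the share of eligible patients missed, and d is the difference in prevalence between screened and missed patients. The article gives neither, so the values below are assumptions.

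| s | d (points) | Bias (points) |
|---|---|---|
| 10% | 10 | 1.0 |
| 20% | 10 | 2.0 |
| 25% | 15 | 3.75, about 3.8 |

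The bias reaches a half-width of 2.3 points when s = 2.3/10 = 23% at d = 10, or s = 2.3/15 = about 15% at d = 15.

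**6. Effect on the interval.** At p = 0.30 and d = 10 points, the nominal 95% interval covers the true value for the stated population about 87% of the time if s = 10%, and about 61% if s = 20%.

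**7. Whether another part of the plan covers the gap.** The weighted stratified sampling in Table 1 concerns the draw of the 400-patient cohort by sex, age, ED and IES-R score from people already enrolled. It cannot restore people who were never screened. The comparison of included and not-included patients could show the gap, but only if unscreened overnight attenders are counted as not included, and the section does not say that they are.

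**The case against.** The strongest reply is that the screening window is openly disclosed and is a reasonable staffing choice, so what remains is loose wording. Much of this stands. Nothing here calls for night staff, and the main remedy is wording.

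A reader might infer that all night arrivals, or a third of eligible patients, are lost. The article does not support that. Patients still present at 08:00 can be screened, and trauma up to a month old is eligible, so an event that happened at night may present by day. Some overnight patients would also be ineligible at any hour, because agitation or altered consciousness that prevents completing the questionnaires is an exclusion.

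A reader might also fault the plan for lacking a correction of the prevalence. Weighting and sensitivity analyses are commonly left to a statistical analysis plan, which is not shown, so their absence is not held against the article.

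Full post-stratification by trauma type from ED registers would be doubtful. Table 2 takes trauma type from the study's own pre-screening questionnaire, and the Background says that ED assessment tends to overlook the traumatic context.

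What the reply does not remove is the mismatch itself. The objective, the design statement and the representativeness claim describe a population that the recruitment procedure cannot reach in full, and the two sections that list reasons for non-inclusion leave this one out.

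**Conclusion.** The mismatch between the stated population and the screening window is certain from the text. Its effect on the prevalence is not: the estimate may be biased, with size and direction unknown. The illustrative 1.0 to 3.8 points rests wholly on an assumed missed share of 10 to 25% and an assumed difference of 10 to 15 points. The low end is below the sampling error of 2.3 to 2.5 points, and the high end is above it.

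It would go too far to say that the prevalence is shown to be biased, or that the cohort's odds ratios are. Missing overnight patients limits how far the predictor results generalise, but does not in itself distort the associations. The secondary 3-month incidence could be affected in the same way as the prevalence.

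**What to change.** 1. In the abstract's discussion, Primary objectives, Methods/design and Participant eligibility, restate the population as eligible patients present in the ED between 08:00 and 24:00, and limit the claims of a consecutive series and of representativeness to that population.
2. In Recruitment process, state that patients who arrived overnight and are still present at 08:00 are screened.
3. In the descriptive analysis section, count unscreened 00:00–08:00 attenders among the not included, with number, age, sex and ED taken from routine registers. Name this source of non-inclusion there and under Challenges. Because registers may not identify recent trauma reliably, say that these counts describe attenders rather than confirmed trauma cases.
4. Optionally, report a prevalence standardised on age, sex and ED as a sensitivity analysis beside the crude value. State that it assumes night and day patients are alike within those strata, which is the point that cannot be checked.

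The cost is a narrower claim, some rewording and a small register extract. The screening hours need not change.

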**Fig. 1 Fig1:**
[figure not shown]
Inclusion stages and follow-up of subjects

### Constitution of the cohort

The prospective cohort study will be conducted on a sub-sample of the participants (Fig. 1). The study biostatistician will arrange a cohort of 400 subjects selected through random sampling stratified by sex (male/female), age (determined by interquartile range of the collected data), investigating ED (1 to 6), and IES-R score (< 12, 12 to 34, > 34). Selected subjects will receive the questionnaires by email or postal mail and will be interviewed by telephone at 3 months (± 15 days) after the index trauma. Mental health professionals (a psychologist, psychiatrist, or resident in psychiatry) who have had special training on the PCL–5 application will conduct the interview.

### Data collection

Table 1 summarizes the different stages of data collection.

**Table 1 Tab1:** Patient inclusion, follow-up, and data collection stages of the study

Steps	Preselection	V1 Inclusion	Establishment of the Cohort	V2 Telephone Follow-up End of the Study
Preselection Criteria Verification *(1)*	X			
Information, Consent Collection and Inclusion		X		
Self-administered questionnaires {IES–R; PDEQ; STAI-Y (A & B forms); AUDIT; Fagerström; QIDS-SR16; SSQ6}		X		
Clinical Data Collection & Self-administered questionnaire (risk factors) *(2)*		X		
Stratified sampling (weighted)			X	
Mailing self-administered questionnaires to subjects to prepare for the telephone interview			X	
Telephone Interview: PCL–5; STAI-Y (A & B forms); AUDIT; Fagerström; QIDS-SR16; SSQ6 (+ back to work time)				X
Intercurrent psychological care (consultation, hospitalization, psychotropic)		X		X

(1) Emergency patient with a recent history of trauma (< 1 month), aged 18 to 70 years, speaks French, and has no guardianship

(2) This self-administered questionnaire consists of PTSD risk factors

Following preselection and written informed consent, patients will be identified as study subjects. At the inclusion phase, he/she will receive self-administered questionnaires to measure acute stress (IES–R), dissociative experiences (PDEQ), anxiety disorder (STAI-Y; A & B forms), social support (SSQ6), alcohol and/or tobacco addiction (AUDIT & Fagerström test), depressive symptoms and suicidality (QIDS-SR16), marital stability, family history of mental health problems and/or instability, socio-economic and familial status, history of trauma exposure, and past psychiatric history. Demographic and physical health-related data will be collected from his/her medical file.

At 3 months after the index date, the cohort study participants will receive self-administered questionnaires by an email {a link with access code to an ePRO (electronic patient reported outcomes) for online completion of questionnaires} or by postal mail (attached with a pre-paid return envelope). The online version of the questionnaires will have to be completed at least one day prior to the telephone interview. These questionnaires will help us assess trauma impact on the patient’s occupational and psychosocial functioning {SSQ6 & STAI-Y (A & B forms)} and PTSD complications and comorbidities such as depression & suicidality (QIDS-SR16), and addiction (AUDIT & Fagerström test).

Additionally, through a telephone interview, a mental health professional (psychologist, psychiatrist, or psychiatric intern) will assess PTSD using the PCL–5 questionnaire and determine whether the subject received any therapeutic care in the 3-month period. The estimated duration of this interview is 15 to 30 min.

Inclusion, follow-up and data collection stages are presented in Table 1.

We will apply the following measures in order to limit the number of dropouts:

Selected patients will receive an email or a postal mail reminding them of their participation in the second stage of the study around 1 month prior to the theoretical date of the interview.

Within 15 days of the interview, we will contact the subject via telephone or email in order to set the date and time for the interview.

In case the first attempt to contact the subject is unsuccessful, we plan three more attempts of telephone call or email. If we fail to establish any (telephone/email) contact up to the intended date of the interview, the subject will be considered as lost to follow-up.

Subject participation in the study will end with the completion of this telephone interview.

Patients with an IES-R score of > 34 will be proposed to consult a specialized healthcare professional (psychiatrist or addictionologist) for the diagnosis and treatment (if necessary) of PTSD or its complications (alcoholism and/or substance abuse, suicidality, and depressive symptomatology).

### Outcome criteria and measure instruments

#### Primary outcome criteria

The primary endpoint for the cross-sectional study is the IES–R score of the subjects reflecting their risk of developing PTSD at inclusion in the ED. An IES-R score > 34 will be considered as a high-risk of subsequent PTSD, an IES-R score of 12–34 as a moderate risk, and an IES-R <  12 a low risk [44, 56, 57]. IES-R is a 22-item self-administered questionnaire composed of three subcomponents: intrusion (8 items), hyperarousal (6 items), and avoidance (8 items). Patients evaluate for each item the experience during the last 7 days on a Likert scale 0 = not at all to 5 = extremely. The total score (from 0 to 88) is the sum of all the evaluations. IES-R has good psychometric characteristics [56–62], and is recommended in France for PTSD surveillance [63]. The IES-R is among the most used scales [64], it is validated in French with a mean completion time of 5 to 10 min [65].

The primary endpoint of the prospective cohort study is the presence or absence of 3-month PTSD defined by PCL-5 (PTSD Check List for DSM-5). PCL-5 is a 20-item self-reported measure. Consistent with the Diagnostic and Statistical Manual of Mental Disorders, Fifth Edition (DSM-5), it assesses 20 symptoms of PTSD. The questionnaire uses “0=not at all” to “4 = extremely” ratings to evaluate each symptom. A probable diagnosis of PTSD is made by considering any item with a score of ≥2 as present and then by adhering to DSM-5 instructions that require at least: 1 item B (questions 1–5), 1 item C (questions 6(− 7), 2 items D (questions 8–14), and 2 items E (questions 15–20). The cut-off score for PCL-5 is ≥33 [66, 67]. This tool has a good sensitivity for a provisional diagnosis of PTSD, and has the advantage to have a shorter completion time (about 5 to 10 min) than the CAPS–IV [16, 19, 20].

#### Secondary outcome criteria

Anxiety disorder will be assessed using the State-Trait Anxiety Inventory (STAI-Y; form A & B) [68, 69] at inclusion and at 3-month follow-up. STAI-Y is a self-report tool that assesses momentary as well as habitual anxiety. It includes two scales of 20 items, each rated from 1 = not at all/almost never to 4 = very much so/almost always [68, 69]. The State-Anxiety subscale (STAI-Y A), assesses the intensity of subjective feelings of tension, worry, apprehension, and nervousness at the current moment. The Trait-Anxiety subscale (STAI-Y B), measures frequency of anxiety vulnerability that includes overall degree of security, confidence, and calmness.

The presence or absence of dissociative experiences will be assessed through the validated French version of Peritraumatic Dissociative Experiences Questionnaire (PDEQ) [64, 70] at inclusion. PDEQ is a self-administered questionnaire designed to assess the presence and intensity of peritraumatic dissociative reactions during or immediately following a potentially traumatic event. In accord with the peritraumatic dissociative symptoms, the questionnaire has 10 corresponding items. For each item, the subject selects the answer most adapted to his/her experience from 1 (not at all true) to 5 (extremely true). The final score is the sum of all the selected answers, varying from 10 to 50, 10 being the minimum signifying absence of dissociative experiences and a score greater than 10 indicates that the patient has dissociative experiences.

At inclusion, we will evaluate patient’s social support as a risk factor and at 3-month follow-up as a psychosocial and occupational consequence of the trauma. For this purpose, we will ask his/her return time to the workplace and use the validated French version of the Social Support Questionnaire 6 (SSQ6) [71, 72]. SSQ6 is a 6-item questionnaire that measures two aspects of perceived social support, i.e. availability and satisfaction. Availability is defined as the individual’s estimation of the number of people who can help him/her if required. Satisfaction is defined as the perceived adequacy between the support received and his/her expectations and needs. For each item, the respondent lists the people (max. 9) he/she can count on in the situation described and expresses his/her degree of satisfaction (from 1 to 6) with regard to this support. We then calculate one score for availability (score N, that varies from 0 to 54), and another for satisfaction (score S, that varies from 6 to 36).

For the assessment of alcoholism and nicotine dependence at inclusion and at 3-month follow-up (as PTSD-related complications), we will use Alcohol Use Disorder Identification Test (AUDIT) and Fagerström test, respectively [73, 74].

The AUDIT consists of 10 questions and screens for risky or harmful use of alcohol. It is the reference for detecting alcohol misuse. Men scoring ≥7 and women scoring ≥6 raise the suspicion of alcohol misuse [73, 75].

The Fagerström test is a quick 6-item test that quantifies patient’s level of nicotine dependence [75]. The score ranges from 0 to 10. Dependency is deemed to be null if the score is from 0 to 2, low from 3 to 4, average from 5 to 6, strong from 7 to 8, and very strong from 9 to 10.

In order to assess depression and suicidal ideation (as risk factors at inclusion), and as PTSD-related complications or comorbidities at 3 months, we will use the Quick Inventory of Depressive Symptomatology (Self-Report) (QIDS-SR16). The QIDS-SR16 is a self-administered questionnaire with 16 items describing the 9 symptom domains of DSM-IV associated with depressive feeling [76–78]. The assessment of depression severity is based on the total score as follows: from 1 to 5, absence of depression; from 6 to 10, slight depression; from 11 to 15, moderate depression; from 16 to 20, severe depression; and from 21 to 27, very severe depression. We will also ask for the number of suicide attempts over the last 3 months.

